#### Secondary confirmatory outcomes

2.4.5

•Changes in global eating psychopathology: Reductions in global eating psychopathology will be investigated using the total score of the EDE-Q (Hilbert et al., 2007). The EDE-Q includes 22 items on four subscales that reliably capture the dimensions of weight concern, shape concern, eating concern, and restraint on a 7-point Likert scale (subscales: .85 ≤ Cronbach's α ≤ .93; overall α = .97; Hilbert et al., 2007).•Changes in the weekly frequency of bulimic behavior and regular eating: The *Weekly Binges Questionnaire* (WBQ; Munsch et al., 2007; Munsch et al., 2019) assesses the frequency of binge eating episodes, compensatory behavior, and regular eating by asking participants to count the number of binge eating episodes, the number of compensatory behaviors, and the number of days with regular eating habits during the last week. Thus, the weekly questionnaires throughout the study period will allow us to monitor the occurrence and frequency of bulimic behaviors and assess changes with a higher temporal resolution. Reminders for the WBQ will be sent via text messages.•Changes in eating-disorder-related daily difficulties: To assess reductions in clinical impairments specific to eating disorders, we will employ the *Clinical Impairment Assessment* scale (CIA; Bohn et al., 2008), which measures overall and domain-specific eating-disorder related impairments (i.e., cognitive, social, and personal). The CIA contains 16 items on a 7-point Likert scale and demonstrated excellent internal consistency (Cronbach's α = .97), construct validity, and sensitivity to change (Bohn et al., 2008).•Changes in well-being: The *World Health Organization-Five Questionnaire* (WHO-5; Bech et al., 2003) will be used to assess changes in general well-being. The WHO-5 consists of five items rated on a 6-point scale and has an excellent internal consistency of Cronbach's α = .92 (Brähler et al., 2007).•Changes in work capacity: In line with the increasing significance of health economic evaluations (Jenkins et al., 2021; Safi et al., 2022; Watson et al., 2018), improvements in work capacity and productivity will be measured based on the *iMTA Productivity Cost Questionnaire* (iPCQ; Bouwmans et al., 2013; Bouwmans et al., 2015). The iPCQ examines long-term (>2 weeks) and short-term (<2 weeks) absences from work and productivity losses as a result of sickness-related restrictions in work efficiency. Test-retest reliability of the iPCQ is excellent concerning the reported number of sick leave days (ICC = .83) and moderate regarding the number of days at work while impeded (ICC = .56) and efficiency rates (ICC = .73; Bouwmans et al., 2013).

#### Secondary exploratory outcomes

2.4.6

•Changes in comorbid depressive symptoms: To capture a possible reduction in comorbid depressive symptoms, we will employ the depression module of the *Patient Health Questionnaire-9* (PHQ-9; Kroenke et al., 2001). The PHQ-9 is a valid self-administered questionnaire that captures the severity of depressive symptoms on nine 4-point Likert-scaled items based on the DSM-IV criteria and has an internal consistency of Cronbach's α = .86 (Kroenke et al., 2001).•Changes in comorbid anxiety symptoms: Comorbid anxiety symptoms will be measured with the *General Anxiety Disorder Scale* (GAD-7; Löwe et al., 2008). The GAD-7 consists of seven items answered on a 4-point scale and is a valid and reliable questionnaire for assessing generalized anxiety disorder symptoms (Cronbach's α = .89).•Changes in self-esteem: Self-esteem improvements will be analyzed as essential treatment target in patients with eating disorders (Linardon et al., 2019). For this purpose, the *Rosenberg Self-Esteem Scale* will be used (RSES; Roth et al., 2008), consisting of 10 items answered on a 4-point scale and showing good internal consistency (α = .88; Roth et al., 2008).•Changes in emotion regulation difficulties: Possible decreases in emotion regulation difficulties following the intervention will be assessed using the *Difficulties in Emotion Regulation Scale* (DERS; Gratz and Roemer, 2004). The DERS consists of 36 items answered on a 5-point scale and has been validated as a reliable measure (subscales: Cronbach's α ≥ .80; overall α =.93).•Use of emotion regulation strategies: The *Heidelberg Form for Emotion Regulation Strategies* (HFERST; Izadpanah et al., 2019) assesses the frequency of emotion regulation strategy use for eight strategies (*rumination, reappraisal, acceptance, problem solving, suppression of emotional expression, suppression of emotional experience, avoidance, social support*). The questionnaire's 28 items are answered on 5-point scales, and the internal consistencies for the subscales range from α = .78 to α = .86 (Izadpanah et al., 2019).•Ecological momentary assessment (EMA): Smartphone-based EMA will be implemented to capture eating disorder symptoms, everyday affect, and emotion regulation with a high ecological validity in daily life. EMA will be conducted for five days at pre- and post-treatment and will consist of five daily signal-contingent and additional event-based assessments after bulimic behaviors. Binge eating episodes and compensatory behaviors will be assessed based on the DSM-5 criteria for BN and previous EMA studies (APA, 2013; Munsch et al., 2009; Schaefer et al., 2020). In line with previous research, we will further measure BN symptoms, including shape and weight concerns (Hilbert et al., 2007) as well as eating-disorder urges (Tasca et al., 2009). The items measuring affect (Watson and Clark, 1994), emotion regulation strategies (Izadpanah et al., 2019), and regulatory difficulties (Lavender et al., 2017), were derived from previous research and established questionnaires (Pruessner et al., 2022).

#### Other measures

2.4.7

•Attitudes towards psychological online interventions: Two subscales of the *Attitudes Towards Psychological Online Interventions Scale* (APOI; Schröder et al., 2015) will be used. The selected subscales consist of eight items rated on a 5-point scale and are validated as reliable measures of perceived technologization threat (Cronbach's α = .64) and anonymity benefits (Cronbach's α = .62) of online interventions (Schröder et al., 2015).•Patient outcome expectancies: Treatment motivation will be assessed using the *Patients' Therapy Expectation and Evaluation Scale* (PATHEV; Schulte, 2008). The PATHEV consists of 16 items answered on a 5-point scale and has been revealed to reliably measure treatment motivation (α > .73; Schulte, 2005).•Negative intervention effects: The *Negative Effects Questionnaire* (NEQ; Rozental et al., 2019) will be used to capture the occurrence of adverse intervention effects. For each of the 32 items of the NEQ, participants answer whether an adverse effect occurred (yes/no), how strong the effect was (0 to 4) and whether they attribute the negative effect on the treatment or something else. Two scores can be obtained, one for the frequency of adverse effects due to treatment, ranging from 0 to 32, and one for the negative impact, ranging from 0 to 128. The NEQ has been established as a valid and reliable measure and has an internal consistency of Cronbach's α = .95 (Rozental et al., 2019).•Use of other healthcare services: To measure access to healthcare as well as the use of other healthcare services, the *Client Sociodemographic Service Receipt Inventory – European Version* (CSSRI-EU; original: Chisholm et al., 2000; Roick et al., 2001) will be used, which is a valid and reliable measure to assess the number and length of different types of healthcare service contacts (e.g., number of therapy sessions and contact with psychotherapists and psychiatrists).•Patient adherence: The log files on the *Selfapy* platform will be employed to capture patient adherence. This includes the number of times and dates a participant logs into the web-based intervention and the number of completed modules. Additionally, participants in the IG will be asked how many times they used the intervention in the study assessments after six and 12 weeks.

### Statistical methods

2.5

Our statistical analyses will consist of four steps: (1) descriptive analyses, (2) confirmatory analyses of our primary outcomes, including sensitivity analyses, (3) analyses of secondary outcomes, including sensitivity analyses, (4) moderator and mediator as well as analyses of the EMA data. All statistical analyses will be conducted using R Statistics (R Core Team, 2021); see the R script in the supplementary materials (Supplement S3).

#### Primary and secondary outcome analyses

2.5.1

For the statistical analyses of the effectiveness of the web-based intervention for patients with BN, growth models within a mixed linear models (MLM) framework will be performed. These have the advantage of considering the multi-level data structure of three repeated assessments (level 1) as nested within patients (level 2) and treating the outcome change as a continuous process. Additionally, MLMs have more power when handling missing data than traditional approaches (Hesser, 2015; Kahn and Schneider, 2013; Tasca and Gallop, 2009). To evaluate whether there is a significant treatment × time interaction effect, we will follow a stepwise procedure by running models of increasing complexity (Kahn and Schneider, 2013). First, a random intercept model without predictors will be conducted, then we will add fixed effects of time (study entrance, 6 weeks, 12 weeks) and treatment (IG vs. CG) into the second model. Finally, the treatment × time interaction will be included to evaluate whether the outcome change differs between the IG and the CG. Likelihood ratio tests and the Akaike Information Criterion will be used to compare the fit of these three models. A significant treatment × time-interaction with more substantial changes in the intervention group compared to the waitlist group will confirm the hypotheses (Raudenbush and Bryk, 2002). The magnitude of treatment effects will be estimated following the suggestions for Cohen's *d* by Feingold, 2009, Feingold, 2013.

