#### Randomization and blinding

2.3.1

Each participant completing the baseline assessment will be randomized by an independent researcher not involved in the project using a computer-based algorithm provided by the online platform *SoSci Survey* (Leiner, 2021) with a 1:1 ratio. Participants will be automatically informed about the randomization result. Therefore, interviews will be conducted blindly, as the clinical interviewers do not know to which group the interviewed participant will be allocated (allocation sequence concealment; Altman and Schulz, 2001). Participants are not explicitly informed that there is an intervention and a control group; instead, they are told that the waiting period for the intervention randomly varies between 0 and 12 weeks. After randomization, each participant will immediately receive an email either including the access code for the intervention (IG) or the information that the intervention will start in 12 weeks (CG).

Group allocation will be masked during the data analyses to minimize possible bias concerning the statistical procedure. For this purpose, an independent researcher will delete all information in the data set indicating the group allocation. Therefore, the evaluator does not know which expression of the group variable represents the IG or the CG.

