### Statistical power and sample size

2.6

Sample size estimations were based on meta-analytic evidence for the effectiveness of psychological interventions for BN (Beintner et al., 2014; Haderlein, 2022; Svaldi et al., 2019). Due to the high heterogeneity of effect sizes ranging from medium to large (Beintner et al., 2014; Haderlein, 2022; Svaldi et al., 2019), the sample size needed to detect at least an effect of medium magnitude was estimated using the R package *powerlmm* (Magnusson, 2018). A power analysis with an effect size of *d* = 0.50, an intraclass-correlation of .40 (Arend and Schäfer, 2019), a power of .80, and an alpha-level of .05 resulted in a required sample of *N* = 152. Further power analyses, including possible dropouts, different effect sizes, and intra-class correlations, can be found in the supplementary materials (Figure S2), strengthening our conclusion that our sample size will be sufficiently large to detect a medium effect under different assumptions.

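### The primary treatment × time test leaves baseline means free in each arm: it is valid, and N = 152 fits it, but at the planned ICC of .40 it has power .80 where baseline adjustment would give about .92

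*Protocol article*

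**What the plan says.** Section 2.5.1 of the protocol article plans growth models in a linear mixed framework that treats the "multi-level data structure of three repeated assessments (level 1) as nested within patients (level 2") and builds up in three steps. The first step is a random intercept model without predictors. The second is to "add fixed effects of time (study entrance, 6 weeks, 12 weeks) and treatment (IG vs. CG) into the second model". The third reads: "Finally, the treatment × time interaction will be included to evaluate whether the outcome change differs between the IG and the CG". A significant interaction favouring the intervention arm confirms the hypotheses.

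Section 2.5.1 specifies neither a baseline covariate nor a common baseline mean. Section 2.5.3 tests for baseline differences between arms and adds any variable that differs significantly as a moderator of the interaction, as a robustness check. That does not adjust the primary test for baseline.

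Section 2.6 gives the design figures: "A power analysis with an effect size of *d* = 0.50, an intraclass-correlation of .40" and "a power of .80, and an alpha-level of .05 resulted in a required sample of *N* = 152". Section 2.3.1 allocates "with a 1:1 ratio", after the baseline assessment has been completed.

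**The concern.** A treatment main effect alongside the interaction makes the model estimate a baseline difference between arms and, in effect, subtract it. Randomisation follows the baseline assessment, so the true baseline difference is zero. Estimating it adds noise to the contrast and removes nothing systematic.

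How much noise depends on the correlation between baseline and week 12. When that correlation is modest, a change score carries more variance than the week-12 score alone. The planned ICC of .40 lies in that region. Precision is at stake: the same patients and the same measurements could give a noticeably more powerful test.

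**Working it through.** **Inputs.** d = 0.50, ICC ρ = .40, power .80, alpha .05 and N = 152 (section 2.6); 1:1 allocation, hence 76 per arm (section 2.3.1); assessments at 0, 6 and 12 weeks and a random intercept (section 2.5.1). Assumed because the article does not state them: two-sided test, total SD of 1 at each wave, normal outcome, no random slope, complete data.

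**Step 1: reproduce the plan.** With three equally spaced complete waves and linear time, the slope over 12 weeks is the week-12 value minus the baseline value. Its variance per patient is 2(1 − ρ) = 2 × 0.60 = 1.20. Then n per arm = 2 × 7.849 × 1.20 / 0.25 = 75.4, rounded up to 76, so N = 152. The standard error is √(2 × 1.20 / 76) = 0.1777 and power is Φ(0.5/0.1777 − 1.96) = .803. Generalised least squares for the full three-wave model with free baseline means gives the same standard error, both for linear time and for the week-12 contrast with categorical time. The stated N therefore matches this test.

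**Step 2: the alternatives at 76 per arm, ρ = .40.**

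- Week-12 score only: variance 1.00, SE √(2/76) = 0.1622, power .869. It would need 63 per arm (N = 126).
- Baseline as covariate: variance 1 − ρ² = 0.84, SE √(2 × 0.84/76) = 0.1487, power .920. It would need 2 × 7.849 × 0.84 / 0.25 = 52.7, so 53 per arm (N = 106), by the same normal approximation that gives 76.
- Mixed model with a common baseline mean: power .920 for the week-12 contrast with categorical time, .931 with linear time.

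Neither 126 nor 106 equals 152, which confirms that section 2.6 sized the free-baseline contrast.

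**Step 3: dependence on the ICC.** The variance ratio of adjusted to planned is (1 − ρ²) / [2(1 − ρ)] = (1 + ρ)/2. Power at 76 per arm:

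| ICC | Planned | Week 12 only | Adjusted | Variance ratio |
|---|---|---|---|---|
| .30 | .74 | .87 | .90 | .65 |
| .40 | .80 | .87 | .92 | .70 |
| .50 | .87 | .87 | .95 | .75 |
| .60 | .93 | .87 | .97 | .80 |
| .70 | .98 | .87 | .99 | .85 |

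For the last row: planned variance 0.60 gives 0.5/√(2 × 0.60/76) = 3.98, and adjusted variance 0.51 gives 4.32.

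**Step 4: other assumptions.**

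- With an assumed independent random-slope variance of 0.2, at ICC .40, power is .74 planned, .80 week 12 only and .86 adjusted. The order does not change.
- If time is categorical and the interaction is tested on 2 degrees of freedom, power under a linear effect is .71 with free baseline means and .88 with a common one.
- With an assumed 20% loss and complete cases only, power is .71 planned against .85 adjusted. With an assumed 30% loss it is .65 against .80.

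**The case against.** The strongest reply is that nothing here is wrong. The hypothesis concerns greater decline, the outcome is defined as change, the test contrasts change, and the sample size fits the test. That stands: this is lost efficiency, with no error and no contradiction. It does not dispose of the point, because under the plan's random-intercept assumptions the alternative is more precise at every ICC below 1 and uses data already collected.

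Four stronger readings are tempting, and the document does not support them.

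- **That regression to the mean or baseline imbalance biases the estimate.** Regression to the mean is equal in expectation in randomised arms and cancels. A chance baseline difference D shifts the change contrast by (ρ − 1)D, which is −0.6D at ρ = .40: partial, and zero on average over randomisations.
- **That change from baseline is always worse than ignoring baseline.** This holds only below ICC .50. Section 2.4.4 cites a test-retest reliability above .71 for these behaviours. That is not a 12-week correlation under treatment, but it shows that .40 is not the only plausible value. At ICC .70 the gain from adjustment is about one percentage point of power.
- **That the week-6 assessment is wasted.** It has zero weight only for linear time with complete data. Section 2.5.1 does not settle how time is coded, and with dropout the mixed model gives week 6 some weight.
- **That the trial is underpowered without the change.** Section 2.6 refers to dropout and other ICC scenarios in a supplementary figure that is not shown. The losses of 20% and 30% above are assumptions.

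A further objection is that the primary outcomes are episode counts, so a normal-theory figure is not a forecast for them. That is fair, and the .92 should be read as illustrative.

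**Conclusion.** The point holds as one of efficiency. The planned test is unbiased and N = 152 is right for it. At the protocol's own ICC of .40, leaving the baseline means free costs about 30% of the effective sample size (variance ratio .70) and gives power .80 where .92 is available, or .93 with linear time. These figures rest on a two-sided .05 test, a random intercept, equal variances, normal data and no missing values. The direction of the gain is secure under the random-intercept model. Its size is not: it is larger at a lower ICC and nearly vanishes in power terms by ICC .70. The change is worth making, but the trial does not fail without it.

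**What to change.** In section 2.5.1, take one of two routes:

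- Constrain the baseline mean to be equal in both arms by dropping the treatment main effect and keeping treatment × time, with the treatment terms set to zero at baseline. The second model in the stepwise comparison then contains time only.
- Use the baseline value as a covariate, with weeks 6 and 12 as outcomes.

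In either case state how time is coded and name the week-12 contrast as the primary test. If a count model is used, apply the same constraint or enter the log baseline count as covariate. If a power figure is quoted, give it over a range of ICCs and describe .92 as illustrative for normal data at ICC .40.

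The cost is a respecified model term and a sentence or two of text. Baseline is already measured before randomisation, so no participant or assessment is added. The change should be dated and recorded before outcomes are analysed by arm.

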#### Missing data and sensitivity analyses

2.5.2

Both completer analyses and intent-to-treat analyses will be conducted, as previous studies on web-based interventions report notable dropout rates (Linardon et al., 2018), and completers might systematically differ from non-completers (Altman et al., 2001). For this purpose, two sensitivity analyses will be run: (1) the conservative last-observation-carried-forward (LOCF) method, employing the last available measurement point of each subject, and (2) the multiple imputations by chained equations (MICE) approach using each participant's Body Mass Index, global eating psychopathology, number of binge-eating episodes determined in the EDE interview, and years since illness onset as predictors.

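### The MICE predictor list omits treatment arm, so read as written this sensitivity analysis shrinks the treatment effect by about the missing fraction; calling LOCF conservative is also unsupported

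*Protocol article*

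**What the plan says.** Section 2.5.1 (Primary and secondary outcome analyses) sets the main analysis: "growth models within a mixed linear models (MLM) framework will be performed", with the hypotheses judged on the treatment × time interaction over baseline, week 6 and week 12.

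Section 2.5.2 (Missing data and sensitivity analyses) expects notable dropout, plans completer and intent-to-treat analyses, and says that "two sensitivity analyses will be run". The first is "the conservative last-observation-carried-forward (LOCF) method, employing the last available measurement point of each subject". The second is MICE, with "Body Mass Index, global eating psychopathology, number of binge-eating episodes determined in the EDE interview, and years since illness onset as predictors". Treatment arm is not named, nor are the primary outcome values at the three assessments. The list is not said to be exhaustive, and section 2.5 refers to an R script in Supplement S3 that is not available here.

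Section 2.4.5 (Secondary confirmatory outcomes) adds a weekly questionnaire, the WBQ, which "assesses the frequency of binge eating episodes, compensatory behavior, and regular eating".

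**The concern.** An imputation model should contain every variable in the analysis model, above all the one whose effect is tested. If arm is absent, the model predicts a missing week-12 value from a pool of both arms. Under randomisation the listed patient characteristics carry essentially no information about arm, so the imputed values show almost no group difference. The completed data then mix observed values that carry the effect with imputed values that do not.

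Section 3.1 (Strengths and challenges) relies on sensitivity analyses to judge the influence of dropout. If MICE disagrees with the mixed model only because arm was left out, the reader cannot tell genuine fragility from an artefact of imputation. The LOCF label has a related problem: it promises a direction of error that the method does not guarantee.

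**Working it through.** **Inputs from the article.** Section 2.6: "A power analysis with an effect size of *d* = 0.50", "an intraclass-correlation of .40", power .80, alpha .05, N = 152. Section 2.3.1: 1:1 allocation. Section 2.5.1: three assessments, scaled here to times 0, 0.5 and 1.

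**Assumptions not in the article.** Random dropout of 10 to 40% at week 12; half of those dropouts also miss week 6; control improvement of 0.3 SD; each listed covariate correlated with the patient intercept.

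**Reproducing N.** In a random-intercept growth model with total variance 1, the residual variance is 1 − 0.40 = 0.60. The sum of squares of time is 0.5² + 0² + 0.5² = 0.5. The SD of a per-person slope is √(0.60/0.5) = 1.095. Per arm, n = 2 × (1.960 + 0.842)² × 1.2 / 0.50² ≈ 75.4, so 76 per arm and N = 152. The plan's figure is reproduced (two-sided alpha, no dropout, no random slope).

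**MICE without arm: expected size.** With three complete values the slope is the week-12 value minus the baseline value, so only the week-12 mean matters. If a fraction m is missing in each arm and is filled from a pool of both arms, the arm means are (1 − m)μ₁ + mμ̄ and (1 − m)μ₀ + mμ̄. Their difference is (1 − m)(μ₁ − μ₀). With 0.50 this gives 0.45, 0.40, 0.35 and 0.30 at m = 10, 20, 30 and 40%.

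**MICE without arm: simulation** (600 trials per setting, 76 per arm, 20 imputations, Rubin's rules). Cells show mean estimate / rejection rate:

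| Dropout, both arms | Four listed predictors only | Plus arm and repeated outcomes | Mixed model, available data |
|---|---|---|---|
| 10% | 0.45 / 0.68 | 0.50 / 0.77 | 0.50 / 0.77 |
| 20% | 0.39 / 0.51 | 0.49 / 0.72 | 0.49 / 0.71 |
| 30% | 0.35 / 0.37 | 0.50 / 0.68 | 0.50 / 0.70 |
| 40% | 0.29 / 0.20 | 0.48 / 0.62 | 0.49 / 0.65 |

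At 30% dropout the mixed model rejects in 0.698 of trials and four-predictor MICE in 0.372. In at least 0.698 − 0.372 = 0.326 of trials, then, the main test is significant and the sensitivity analysis is not, although the effect is real.

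**Which omission matters.** At 30% dropout:
- four predictors only: 0.351
- adding repeated outcomes without arm: 0.357
- adding arm alone: 0.499
- adding both: 0.500

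Arm accounts for nearly all the bias. The repeated outcomes mainly add a little precision (rejection 0.678 against 0.672 with arm alone).

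**LOCF direction.** Under these assumptions half of the dropouts carry forward baseline (no change) and half carry forward week 6 (half the change). An arm's expected change is therefore multiplied by 1 − m + 0.25m = 1 − 0.75m. With a control change of 0.3 and an intervention change of 0.8:
- Equal 20% dropout: 0.50 × 0.85 = 0.425, an attenuation (simulated 0.42).
- Intervention 30%, waitlist 10%: 0.8 × 0.775 − 0.3 × 0.925 = 0.34, an attenuation (simulated 0.35).
- Intervention 10%, waitlist 40%: 0.8 × 0.925 − 0.3 × 0.70 = 0.53, above the true 0.50 (simulated 0.53).

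If controls improve by 0.6 SD, the last setting gives 1.1 × 0.925 − 0.6 × 0.70 = 0.60 (simulated 0.61). With no true effect, the 10%/40% setting gave two-sided type I error of 0.066 (control improvement 0.3 SD) and 0.125 (0.6 SD).

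**The case against.** The strongest objection is that the article is condensed. It does not say that only these four variables enter, chained equations normally also use the other incomplete variables, and Supplement S3 may specify the whole model. This stands as a limit: a reader might infer that arm is definitely excluded, and the documents do not establish that. It does not clear the text. Arm is fully observed, so it enters only if someone puts it in, and the one list given leaves it out. If the script includes arm, the article describes the analysis incorrectly.

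It can also be said that global eating psychopathology is not stated to be the baseline value, and that later values would carry treatment information. That is true, but the EDE-Q supplies both that score and the primary counts at the same visits, so a missed questionnaire loses both. By analogy, repeated outcome values without arm barely reduced the bias above.

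Other tempting readings go too far:
- *Dropout is otherwise unexamined.* The main mixed model uses all available assessments, and completer analyses are planned.
- *The missing repeated outcomes cause the bias.* Under random dropout they do not.
- *LOCF is always anti-conservative.* It attenuates under equal or higher intervention-arm dropout, so the label is unsupported rather than always wrong. An effect that is large at week 6 and mostly lost by week 12 would also make LOCF overstate the result, but nothing in the article points to that course.
- *LOCF must be replaced by reference-based or delta-adjusted imputation.* That is a reasonable preference, not the correction of an error.

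Masking is no obstacle. Section 2.3.1 keeps a group variable and hides only which code is which, so the coded arm can be used.

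**Conclusion.** The point holds in a limited form. Followed as written, the MICE analysis pulls the treatment × time effect toward zero by about the missing fraction: from 0.50 to roughly 0.45, 0.39, 0.35 and 0.29 at 10, 20, 30 and 40% dropout. These sizes rest on assumed dropout rates, random dropout and a literal reading of the predictor list; the article gives no rate. At 10% the shift is small, and at 30% or more it could plausibly overturn the robustness conclusion. The error is toward zero, so on this count it cannot create a false positive. The primary mixed-model test, its decision rule and N = 152 are untouched. The unconditional description of LOCF is not justified. Severity: should-fix.

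**What to change.** In section 2.5.2, and in the script if it differs:

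1. State that the imputation model includes the coded treatment arm, or that imputation is done separately by arm. This removes the bias.
2. Include binge-eating and compensatory-behavior counts at baseline, week 6 and week 12, mainly for precision and to make the missing-at-random assumption more plausible. The weekly WBQ counts may be added as auxiliaries.
3. Keep the four listed variables as auxiliaries, and say at which assessment global eating psychopathology is taken.
4. Delete *conservative* for LOCF, or qualify it by saying that its direction depends on differential dropout and on improvement in the waitlist arm.

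The cost is a few sentences and a few lines of R. No new data are needed, and neither the sample size nor the primary analysis changes. If Supplement S3 already includes arm, only the text needs correcting.
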